### Participant timeline {13}

See Tables 2, 3, 4, and 5 for the participant schedule of activities and visit timeline.

**Table 2 Tab2:** Schedule of activities—women in group A

Visit #	1	2	3	4	5	6	7 ^a^	8	9	10	11^a^	EE
**Visit timing**^**p**^		**Dose 1**	**Dose 1** ** + 7 days**	**Dose 1 + ** **28 days**	**Dose 2**	**Dose 2 + ** **7 days**	**Dose 2 + ** **21 days**	**Dose 2 + ** **28 days**	**Pregnancy completion/** **termination**	**PP 1 + 42**	**Dose 1 + ** **365 days**	**Early** **Exit**
**Visit day and window**	** − 28 to 1**	**D1**	**D8 ± 3 days**	**D29 ± 7 days**	**D57** ** − 14 days, + 28 days**	**D64 ± 3 days**	**D78 ± 3 days**	**D85 ± 7 days**	**PP 1** ^b^ ** + 2 days**	**PP 43** ^c^ ** ± 14 days**	**Dose 1 + 365 ± 28 days**	
**Visit type**	Screening	**DOSE 1 group A**	Safety	Safety	**DOSE 2 group A**	Safety	Immuno	Safety	Safety and immuno	Safety	Safety and immuno	Early exit
Assessment of understanding	•											
Written informed consent (ICF) ^d^	•											
Inclusion/exclusion criteria	•	•										
Demographics ^**e**^	•											
Medical and obstetric history ^f^; pre-pregnancy and pre-study meds	•											
Physical examination ^f^	•				•					•		•
Obstetric exam ^f^	•	•			•				•			•^o^
Targeted physical exam ^f^		•	•	•		•	•	•			•	
Vital signs ^f^ incl. body temperature	•		•	•		•	•	•	•	•	•	•
Urine pregnancy test ^g^	•											
Hematology, chemistry ^g^	•											
Urine dipstick/urinalysis ^g^	•	•		•	•			•				
Syphilis, HIV, hepatitis B and C, malaria screening^g^	•											
Obstetric ultrasound ^h^	•	•^h^						•				•^o^
Biometric scan	•	•	•	•	•	•	•	•	•	•	•	•
Contact information	•	•	•	•	•	•	•	•	•	•	•	•
Randomization		•										
Pre-vaccination symptoms ^i^												
Vaccination		•			•							
30 min post-vaccination observation ^j^		•			•							
Solicited AE collection ^k^		•	•		•	•						
Unsolicited AE collection ^k^		•	•	•	•	•	•	•				
Distribution of participant diary, rulers and thermometers ^k^		•			•							
Participant diary review by site staff			•			•						
Adverse maternal, fetal outcomes		•	•	•	•	•	•	•	•	•		
SAE recording		•	•	•	•	•	•	•	•	•	•	•
Concomitant medications ^l^	•	•	•	•	•	•	•	•	•	•	•	•
Delivery history ^m^									•			
Post pregnancy physical examination ^m^									•			
Laboratory assessments^n^									•			
Acceptability questionnaire									•	•		•
Group A immunology subset supplemental procedures (*N* = 150)	**1**	**2**	**3**	**4**	**5**	**6**	**7**	**8**	**9**	**10**	**11**	
Humoral immunogenicity sample (serum)							•		•			
Cord blood sample									•		•	
Breast milk sample (*N* = 50)										•		

pre-dose;

pre- and post-dose

^a^Visits 7 and 11 for group A immunology subset participants only

^b^PP 1 refers to the day of pregnancy completion/termination. Visit 9 (PP 1) should occur on the day of pregnancy completion/termination or within 2 days

^c^Visit 10 (PP 43) scheduled to occur at routine 6 week post-partum visit. For women from group A not part of the immunogenicity subset, this visit will be the end of the trial

^d^Must be signed before first study-related activity

^e^Maternal demographic information to be collected at screening includes date of birth, race/ethnicity, education level, geographical location/residence, occupation, household size (number of persons living in the same home), and international travel history

^f^Information to be collected for medical and obstetric history, physical exams, and vital signs is specified in the protocol

^g^Urine dipstick for protein and glucose will be performed at these visits. If results 1 + or greater, then additional work-up for pre-eclampsia or gestational diabetes may be warranted

^h^Ultrasound not required at visit 2 if screening (visit 1) ultrasound completed within past 10 days and no other indication for ultrasound

^i^Investigator must check for acute illness or body temperature ≥ 38.0 °C at the time of vaccination. In such cases, the participant may be vaccinated at later time point

^j^Participants will be closely observed for a minimum of 30 min post-vaccination

^k^In all women of group A, solicited AEs (reactogenicity) and unsolicited AEs will be assessed 7 days post each dose and 28 post each dose respectively

^l^Includes any medical treatment/medications given to the mother during delivery (e.g., antibiotic prophylaxis)-specifying names of medications administered

^m^Information to be collected for delivery history and post-pregnancy examination is specified in the protocol

^n^Any routine laboratory assessment performed at time of delivery and other laboratory tests as medically indicated

^o^Not required if participant is not pregnant

^p^In case pregnancy completion/termination in a group A pregnant woman occurs prior to receipt of dose 2, visits 9 and 10 should be performed: visit 10 being relative to visit 9 (2 day window). Visit 5 (dose 2 vaccination with a window of – 14 days, + 28 days) should in this case be performed after visit 9, with visits 6 and 8 being relative to actual dose 2 receipt (visit 5). All of these visits should be captured in RedCap cloud in addition to source documentation. Reactogenicity data (diary completion) should still be performed following dose 2 for group A women that have a pregnancy completion/termination prior to receipt of dose 2

**Table 3 Tab3:** Schedule of activities—women in group B

Visit #	1	2	3	4	5	6	7	8	9^a^	10^n^	11 ^a^	EE
**Visit timing**^**p**^		**Randomiz-ation (D1)**	**D1 + 28 days**	**D1 + 56 days**	**D1 + 12 weeks**	**Pregnancy completion/** **termination**	**Dose 1**	**Dose 2**	**Dose 2 + ** **21 days**	**Dose 2 + ** **28 days**	**Dose 1 + ** **365 days**	**Early** **exit**
**Visit day and window**	**-28 to 1**	**D1**	**D29 ± 7 days**	**D57** ** − 14 days, + 28 days**	**D85 ± 7 days**	**PP 1** ^b^ ** + 2 days**	**PP 43** ^c^ ** + 28 days**	**PP 99** **-14 days, + 28 days**	**PP 120** ** ± 14 days**	**PP 127** ** ± 3 days**	**Dose 1 + 365 ± 28 days**	
**Visit type**	Screening	**Random-ization**	Safety	Safety	Safety	Safety and immuno	**DOSE 1 group B**	**DOSE 2 group B**	Safety and immuno	Safety	Safety and immuno	Early exit
Assessment of understanding	•											
Written informed consent (ICF) ^d^	•											
Inclusion/exclusion criteria	•	•										
Demographics ^**e**^	•											
Medical and obstetric history ^f^ and prestudy meds	•											
Physical examination ^f^	•						•	•				•
Obstetric exam ^f^	•	•				•						•^o^
Targeted physical examination ^f^		•	•	•	•				•	•	•	
Vital signs ^f^ incl. body temperature	•	•	•	•	•	•			•	•	•	•
Urine pregnancy test ^g^	•											
Hematology, chemistry ^g^	•											
Urine dipstick/urinalysis ^g^	•	•	•	•	•							
Syphilis, HIV, hepatitis B and C, malaria screening ^g^	•											
Obstetric ultrasound ^h^	•	•^h^			•							•^o^
Biometric scan		•	•	•	•	•	•	•	•	•	•	•
Contact information	•	•	•	•	•	•	•	•	•	•	•	•
Randomization		•										
Pre-vaccination symptoms^i^												
Vaccination							•	•				
30 min post-vaccination observation ^j^							•	•				
Adverse maternal, fetal outcomes		•	•	•	•	•	•					
SAE recording		•	•	•	•	•	•	•	•	•	•	•
Concomitant medications ^k^	•	•	•	•	•	•	•	•	•	•	•	•
Delivery history ^l^						•						
Post pregnancy physical examination ^l^						•						
Laboratory assessments ^m^						•						
Group B immunology subset supplemental procedures (*N* = 150)	**1**	**2**	**3**	**4**	**5**	**6**	**7**	**8**	**9**	**10**	**11**	EE
Humoral immunogenicity sample (serum)									•		•	
Breast milk sample (*N* = 10)												

pre-dose;

pre- and post-dose

^a^Visits 9 and 11 for group B immunology subset participants only

^b^PP1 refers to the day of pregnancy completion/termination. Visit 6 (PP1) should occur on the day of pregnancy completion/termination or within 2 days

^c^Visit 7 (PP 43) scheduled to occur at routine 6 week post-partum visit

^d^Must be signed before first study-related activity

^e^Maternal demographic information to be collected at screening includes: date of birth, race/ethnicity, education level, geographical location/residence, occupation, household size (number of persons living in the same home), and international travel history

^f^Information to be collected for medical and obstetric history, physical exams, and vital signs is specified in the protocol

^g^Urine dipstick for protein and glucose results will be performed at these visits. If results are 1 + or greater, then additional work-up for pre-eclampsia or gestational diabetes may be warranted

^h^Ultrasound not required at visit 2 if screening (visit 1) ultrasound completed within past 10 days and no other indication for ultrasound

^i^Investigator must check for acute illness or body temperature ≥ 38.0 °C at the time of vaccination. In such cases, the participant may be vaccinated at later time point

^j^Participants will be closely observed for a minimum of 30 min post-vaccination

^k^Includes any medical treatment/medications given to the mother during delivery (e.g., antibiotic prophylaxis)-specifying names of medications administered

^l^Information to be collected for delivery history and post-pregnancy examination is specified in the protocol

^m^Any routine laboratory assessment performed at time of delivery and other laboratory tests as medically indicated

^n^Visit 10: for women not part of the immunogenicity subset this visit will be the end of the trial

^o^Not required if participant is not pregnant

^p^If pregnancy completion/termination in a group B woman occurs prior to performing all in-pregnancy protocol visits, these missed visits will not be considered as protocol deviations

**Table 4 Tab4:** Schedule of activities—women From Umurinzi

Visit #	1	2	3	4	5	EE
**Visit timing**		**Dose 2**	**Dose 2 + 28 days**	**Pregnancy completion/termination**	**PP 1 + 42 days**	**Early** **exit**
**Visit day and window**	** − 28 to 1**	**D57** ** − 14 days, + 28 days**	**D85 ± 7 days**	**PP 1** ^a^ ** + 2 days**	**PP 43** ^b^ ** ± 14 days**	
**Visit type**	Screening	**Dose 2**	Safety	Safety and immuno	Safety	Early exit
Assessment of understanding	•					
Written informed consent (ICF) ^c^	•					
Inclusion/exclusion criteria	•					
Demographics ^d^	•					
Medical and obstetric history ^e^; pre-pregnancy and pre-study meds	•					
Physical examination ^e^	•				•	•
Obstetric exam ^e^	•	•		•		•^m^
Targeted physical exam ^e^		•	•			
Vital signs ^e^ incl. body temperature	•		•	•	•	•
Urine pregnancy test ^f^	•					
Hematology, chemistry ^f^	•					
Urine dipstick/urinalysis ^f^	•	•	•			
Syphilis, HIV, hepatitis B and C, malaria screening ^f^	•					
Obstetric ultrasound ^g^	•		•			•^m^
Biometric scan	•	•	•	•	•	•
Contact information	•	•	•	•	•	•
Pre-vaccination symptoms ^h^						
Vaccination		•				
30 min post-vaccination observation^i^		•				
Adverse maternal, fetal outcomes		•	•	•	•	
SAE recording		•	•	•	•	•
Concomitant medications ^j^	•	•	•	•	•	•
Delivery history ^k^				•		
Post pregnancy physical examination ^k^				•		
Laboratory assessments ^l^				•		

pre-dose;

pre- and post-dose

^a^PP 1 refers to the day of pregnancy completion/termination. Visit 4 (PP 1) should occur on the day of pregnancy completion/termination or within 2 days

^b^Visit 5 (PP 43) scheduled to occur at routine 6 week post-partum visit

^c^Must be signed before first study-related activity

^d^Maternal demographic information to be collected at screening includes: date of birth, race/ethnicity, education level, geographical location/residence, occupation, household size (number of persons living in the same home), and international travel history

^e^Information to be collected for medical and obstetric history, physical exams, and vital signs is specified in the protocol

^f^Urine dipstick for protein and glucose will be performed at these visits. If results are 1 + or greater, additional work-up for pre-eclampsia and gestational diabetes may be warranted

^g^Ultrasound not required at visit 2 if screening (visit 1) ultrasound completed within past 10 days and no other indication for ultrasound

^h^Investigator must check for acute illness or body temperature ≥ 38.0 °C at the time of vaccination. In such cases, the participant may be vaccinated at later time point

^i^Participants will be closely observed for a minimum of 30 min post-vaccination

^j^Includes any medical treatment/medications given to the mother during delivery (e.g., antibiotic prophylaxis)-specifying names of medications administered

^k^Information to be collected for delivery history and post-pregnancy examination is specified in the protocol

^l^Any routine laboratory assessment performed at time of delivery and other laboratory tests as medically indicated

^m^Not required if participant is not pregnant

**Table 5 Tab5:** Schedule of activities—neonates/infants from groups A, B, and Umurinzi

Visit #	1 ^a^	2 ^b^	3
**Visit timing**	**Pregnancy completion/termination**	**PP1 + 42 days**	**PP1 + 98 days**
**Visit day and window**	**PP 1** ** + 2 days**	**PP 43** ** ± 14 days**	**PP 99 ± 14 days**
**Visit type**	Safety	Safety	Safety and immuno
Fetal monitoring during labor^c^	•		
Birth outcome^d^	•		
Apgar score^e^	•		
Neonatal physical exam^f^	•		
Medication^g^	•	•	•
Nutrition^h^	•	•	•
Infant physical exam ^f^		•	•
Adverse neonatal/infant outcomes	•	•	•
SAE collection	•	•	•
Humoral immunogenicity sample (serum)^i^			•

^a^Visit 1 (PP 1) should occur on the day of pregnancy completion or within 2 days

^b^Informed consent for any study procedures to be performed for infants ≥ 28 days of age will be obtained from mother at enrolment

^c^Record key findings of fetal monitoring such as fetal position at delivery, gestational age, complications, fetal heart rate, and uterine contractions during labor

^d^Live birth, stillbirth, neonatal death, parity

^e^Measured at 1, 5, and 10 min

^f^Information to be collected for neonatal physical examination and infant physical examination is specified in the protocol

^g^Any medical or intervention given to the neonate (e.g., antibiotic treatment, exchange transfusion, intravenous fluids, steroids or other immunosuppressive therapies, herbal remedies, respiratory support)

^h^Type of feeds (e.g., breast milk (mother/donor), formula feeding, parenteral nutrition, mixed feeding) and their respective start and stop times should be recorded in months of age

^i^Blood sample (1 mL) of 75 infants born to women from the group A immunology subset

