**Secondary**	
• Assess safety **in pregnant women** randomized to receive the 2-dose Ebola vaccine regimen (Ad26.ZEBOV, MVA-BN-Filo group A) and in control women (unvaccinated pregnant women (group B))	• Frequency and relatedness of all SAEs in women from randomization until study end
• Assess safety **in neonates/infants born** to women randomized to receive the 2-dose Ebola vaccine regimen (Ad26.ZEBOV, MVA-BN-Filo (group A)) and in neonates/infants born to control women (unvaccinated pregnant women (group B))	• Frequency and relatedness of all SAEs in the newborns from birth until study end
• Assess the **reactogenicity** and unsolicited AEs of the 2-dose Ebola vaccine regimen (Ad26.ZEBOV, MVA-BN-Filo) in all vaccinated pregnant women (group A)	• Reactogenicity, defined as local and systemic solicited AEs occurring within 7 days after each dose, and unsolicited AEs within 28 days after each dose: ○ Frequency, grade, duration and causality for solicited systemic AEs and unsolicited AEs ○ Frequency, grade and duration for solicited local AEs
• Describe all pregnancy outcomes	• Pregnancy outcomes (example: normal delivery, Caesarian Section)
• Assess the **immunogenicity** of the 2-dose Ebola vaccine regimen (Ad26.ZEBOV, MVA-BN-Filo) in 150 pregnant women who are anticipated to receive both vaccine doses within the course of their pregnancy (a subset of the 1000 pregnant vaccinated women from group A) compared to 150 non-pregnant women vaccinated after delivery (a subset of group B)	• Anti-EBOV GP binding antibody concentrations, in ELISA units/mL (FANG ELISA) from: ○ Blood samples taken at pre-dose 1, 21 days post-dose 2, at delivery (group A subset only), and 1 year post-dose 1 ○ Cord blood if feasible from women in the group A subset
• Assess **persistence of maternal antibodies** in 75 infants born to women from the group A subset	• Anti-EBOV GP binding antibody concentrations, in ELISA units/mL (FANG ELISA) from a blood sample taken at 14 weeks of age

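### Table 2 marks cord blood instead of serum at the group A one-year visit, contradicting Table 1 and its own description of that visit

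*Protocol article*

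**What the plan says.** Table 1 (Outcomes {12}, secondary objectives) defines the immunogenicity endpoint as antibody concentrations from "Blood samples taken at pre-dose 1, 21 days post-dose 2, at delivery (group A subset only), and 1 year post-dose 1". The bracketed restriction attaches to delivery alone, so the one-year serum belongs to both subsets. The endpoint serves a comparison of 150 group A women, "compared to 150 non-pregnant women vaccinated after delivery (a subset of group B". Cord blood is a separate item, "Cord blood if feasible from women in the group A subset", with no one-year time point.

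Table 2 (Participant timeline {13}) is the group A schedule. It times visit 11 at "Dose 1 + 365 ± 28 days" and types it as both a safety and an immunology visit. Footnote a reads "Visits 7 and 11 for group A immunology subset participants only". In the block of supplemental procedures for the immunology subset, the row "Humoral immunogenicity sample (serum" carries marks at visits 7 and 9. The row beneath it, "Cord blood sample", carries marks at visits 9 and 11.

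Table 3, the group B schedule, marks serum at visits 9 and 11. There, visit 9 is 21 days after dose 2 and visit 11 is one year after dose 1.

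**The concern.** Read as printed, Table 2 asks for a sample at visit 11 that cannot exist and omits the one that the endpoint needs. The visit is held only for the immunology subset, so this mark is the only immunology procedure it contains.

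A schedule of activities is the part of a protocol from which visit checklists and sample kits are prepared, so a mark in the wrong row can pass into practice. At stake is the one-year group A antibody concentration. Three serum times are shared by the two groups: before dose 1, 21 days after dose 2, and one year after dose 1. Only the last shows how antibody persists in women vaccinated during pregnancy compared with women vaccinated after delivery. A draw missed at one year cannot be recovered later, and the article plans no imputation (Statistical methods {20c}).

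**Working it through.** No sample size, power or error-rate figure bears on this point, so the check sets the tables side by side. Each row of the Table 2 and Table 3 subset blocks was read as a label, eleven visit columns and an early-exit column (1 + 11 + 1 = 13 cells). All the subset rows have 13 cells, so the marks line up with their visits.

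| Sample | Table 1 | Table 2, group A | Table 3, group B |
|---|---|---|---|
| Serum before dose 1 | both groups | no mark visible | no mark visible |
| Serum 21 days after dose 2 | both groups | visit 7 | visit 9 |
| Serum at delivery | group A only | visit 9 | none, as expected |
| Serum 1 year after dose 1 | both groups | **not marked** | visit 11 |
| Cord blood | group A, if feasible | visit 9 **and visit 11** | no such row |

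**Could visit 11 coincide with delivery?** The window opens at 365 − 28 = 337 days after dose 1, and 337 / 7 ≈ 48 weeks. Dose 1 is given at day 1 to a woman whose pregnancy has already been confirmed by ultrasound. That pregnancy will have ended well before 48 weeks have passed, so the cord blood mark at visit 11 cannot be carried out.

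**Does the pattern suggest a cause?** After dose 1, Table 1 requires three group A serum samples and Table 2 marks two, so 3 − 2 = 1 is missing, at visit 11. The cord blood row has two marks where one is possible, so 2 − 1 = 1 is surplus, also at visit 11 and in the row directly below. For group B, Table 1 requires two serum samples after dose 1 and Table 3 marks both. One mark set one row too low accounts for the whole discrepancy.

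**Could missing symbols explain it?** The special symbols for pre-dose, and for pre- and post-dose, do not appear in the copy of the tables read here. That probably explains the empty serum cell before dose 1, which is not counted as an error. It does not explain visit 11: no dose is given there, the group B one-year serum is shown with the ordinary mark, and a lost symbol cannot create an ordinary mark in the cord blood row.

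**Size if Table 2 were followed literally.** Group A would have 0 of 150 one-year values and group B up to 150 of 150. Of the two between-group comparisons after vaccination (21 days after dose 2, and one year), one would be lost and one kept.

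**The case against.** The strongest reply is that no one need be misled. Table 1 asks for "at delivery (group A subset only), and 1 year post-dose 1", Table 2 types visit 11 as an immunology visit, and footnote a keeps it for the immunology subset. All three point to a serum draw. Because the printed instruction is impossible, staff are likely to notice it and take serum.

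The article also condenses a full protocol (version 2.0, July 8, 2020) that is not shown and to which its table footnotes refer. Recruitment began on 6 October 2020, so one-year visits began around October 2021, before the article appeared on 2022-06-20. Sites were therefore not working from this table when those visits began.

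Much of this stands. A reader might infer from Table 2 that the trial has no group A one-year value and that the persistence comparison is lost. The documents do not support that: they show a contradictory schedule, not a missed sample, and whether the full protocol carries the same slip is unknown. A reader might also count the empty serum cell before dose 1 as a second omission, which a lost symbol probably explains.

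The contradiction itself remains. The article prints both the endpoint time points and the schedule in full, and they disagree, so nothing is being left to another document. Recruitment was expected to end around January 2022, which puts the last one-year visits around January 2023. A check at publication could still have mattered for later enrollees.

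**Conclusion.** Table 2 is wrong at group A visit 11. It contradicts Table 1, differs from Table 3 where Table 1 requires the same sample, and conflicts with its own visit type and footnote. The consequence is conditional: if sites followed the table literally, up to 150 group A one-year concentrations would be missing and the one-year comparison with group B could not be made.

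The reach is limited to one time point of a secondary endpoint that is summarised descriptively with no formal test. The comparison 21 days after dose 2, the delivery sample, the primary maternal and infant outcomes and the sample size are untouched.

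The conclusion assumes that the published table has its marks where they were read here. If the typeset table shows serum at visit 11, the point falls away, so that should be checked first. It is worth correcting because the correction is easy and a missed sample would be irrecoverable.

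**What to change.** Reconcile Table 2 with Table 1. Move the visit 11 mark from the cord blood row to the serum row. After dose 1, the group A schedule then shows serum at visits 7, 9 and 11 and cord blood at visit 9 only. Confirm that the pre-dose 1 serum symbol is present in the typeset table.

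Check the schedule in the full protocol, the site visit checklists and the sample-collection instructions for the same slip. If any of them repeats it, send sites a short note and establish how many group A one-year serum samples were drawn, so that the report can state the number available at that time point.

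The cost is one table correction and one document check. The design, the sample size and the analysis do not change.

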**Primary**	
• Assess **adverse maternal/fetal outcomes in pregnant women** randomized to receive the 2-dose Ebola vaccine regimen (Ad26.ZEBOV, MVA-BN-Filo (group A)) and in control women (unvaccinated pregnant women (group B))	• Frequency of maternal death, spontaneous abortion, stillbirth, pathways to preterm birth (premature preterm rupture of membranes, preterm labor, insufficient cervix, provider initiated preterm birth), pre-eclampsia/eclampsia, antenatal bleeding and post-partum hemorrhage from randomization until 6 weeks post-completion/termination of pregnancy
• Assess **adverse neonatal/infant outcomes in neonates/infants** born to women randomized to receive the 2-dose Ebola vaccine regimen (Ad26.ZEBOV, MVA-BN-Filo (group A)) and in neonates/infants born to control women (unvaccinated pregnant women (group B))	• Frequency of major congenital malformations, small for gestational age (SGA), low birth weight, preterm birth, neonatal death, and failure to thrive in infants measured from birth until 14 weeks of age

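### The visit that closes the 6-week maternal endpoint may fall at 4 weeks in group A but not before 6 weeks in group B

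*Protocol article*

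**What the plan says.** Table 1 (Outcomes {12}) sets one period for the primary maternal/fetal endpoint in both arms: "from randomization until 6 weeks post-completion/termination of pregnancy". The schedules are in Participant timeline {13}, where "PP 1 refers to the day of pregnancy completion/termination", so days after delivery equal the PP day minus 1.

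- **Group A (Table 2).** Visit 10 is at PP 43 ± 14 days. It is the last column marked for adverse maternal/fetal outcomes. Footnote c describes it as "scheduled to occur at routine 6 week post-partum visit" and then says: "For women from group A not part of the immunogenicity subset, this visit will be the end of the trial". The 150 women in the immunogenicity subset also have visit 11, which has an SAE mark but no maternal-outcome mark.
- **Group B (Table 3).** "Visit 7 (PP 43) scheduled to occur at routine 6 week post-partum visit". Its window is PP 43 + 28 days, with no minus side, and it is the last column marked for adverse maternal/fetal outcomes. Group B women then continue, with SAE recording, to PP 127 ± 3 days: "Visit 10: for women not part of the immunogenicity subset this visit will be the end of the trial".
- **Deliveries before dose 2 (Table 2, footnote p).** In these group A women visit 5 follows delivery, and visits 6 and 8 are timed from the actual second dose. All three visits carry the maternal-outcome mark.
- **Infants (Table 5).** Visit 3 is at PP 99 ± 14 days. The table schedules no maternal-outcome collection.
- **Analysis.** Safety is analysed on all randomized women (Statistical methods {20a}), and missing data are not imputed ({20c}).

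**The concern.** One endpoint with one closing time should be ascertained to that time in both arms. Here the earliest permitted closing visit is two weeks short of the endpoint in group A and exactly at the endpoint in group B. If an event falls after an early visit 10 but within 6 weeks, the group A schedule has no later point, for most women, at which it would be recorded. The matching event in a group B woman falls before her closing visit.

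Any loss therefore runs in one direction, towards fewer events in vaccinated women. Section {6b} explains that the control group is needed because robust background rates are lacking, and Objectives {7} says the study is meant to support a label change. The side-by-side table of frequencies is the main result. The absence of a formal test does not remove the need for equal ascertainment.

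**Working it through.** The protocol article gives no figure for this point. Its sample-size figures reproduce (1 − 0.999^1000 = 63.2%, stated 63%; 1 − 0.05^(1/1000) = 0.299%, stated 0.3%) and are not affected.

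**1. Windows, in days after delivery (PP day − 1).**

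| Visit | Window | PP days | Days after delivery |
|---|---|---|---|
| Endpoint closes | 6 weeks | PP 43 | 42 |
| Group A visit 10 | PP 43 ± 14 | 29 to 57 | 28 to 56 |
| Group B visit 7 | PP 43 + 28 | 43 to 71 | 42 to 70 |
| Group B visit 10 | PP 127 ± 3 | 124 to 130 | 123 to 129 |
| Infant visit 3 | PP 99 ± 14 | 85 to 113 | 84 to 112 |

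**2. Largest permitted shortfall.** Group A: 42 − 28 = 14 days, or 14/42 = 33% of the post-partum part of the endpoint. Group B: 42 − 42 = 0. The endpoint starts at randomization, so the share of the whole endpoint period is smaller than 33%.

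**3. Who is affected.** Visit 10 ends the trial for nominally 1000 − 150 = 850 group A women. Some of those who deliver before dose 2 must be taken off, because visits 6 and 8 may bring them back after visit 10. The document does not give their number. The 150 subset women stay in the trial, but visit 10 is generally their last marked maternal-outcome visit too.

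**4. Average shortfall under an even spread (assumption).** If visits fell evenly on the 29 days PP 29 to PP 57, then 14/29 = 48% would precede PP 43. The mean loss over all women would be (1 + 2 + … + 14)/29 = 105/29 = 3.6 days. Visits tied to routine 6-week care would probably cluster nearer PP 43, so this is likely to be high.

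**5. Size in events, for maternal death.** Sample size {14} cites 210 per 100,000 live births, about 2.1 per 1000. The share of these deaths that falls in days 29 to 42 is not given. I take 5% to 33% as an assumed range.

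- Every group A visit on its earliest day: 2.1 × 0.05 = 0.1 to 2.1 × 0.33 = 0.7 deaths unseen per 1000.
- Even spread, pro rata: multiply by 3.6/14 = 0.26, giving about 0.03 to 0.18 per 1000.

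No rates are given for post-partum pre-eclampsia/eclampsia or late haemorrhage, so those components cannot be sized from the document.

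**6. After the fix.** If the last maternal ascertainment cannot precede PP 43, the minimum is 42 days in both arms and the gap goes from 14 days to 0.

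**The case against.** The strongest reply is that PP 29 is the edge of a tolerance and not the plan. Footnote c in each table ties the visit to the same routine 6-week appointment, so most group A women should be seen close to PP 43. A reader might infer that the endpoint is cut short throughout the vaccinated arm. The documents do not support that: early closure is permitted, not scheduled.

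Four further points stand in part.

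- **Later contacts exist.** Footnote p gives some women who deliver before dose 2 marked outcome visits after visit 10. Section {18a} allows outcomes to be taken from medical records, and a mother's death would probably come to light at the infant's PP 99 visit. It is therefore too strong to say that nothing can be learned after visit 10. None of these routes is a scheduled maternal ascertainment through PP 43 for the remaining women.
- **Controls can be lost too.** Group B women can withdraw or miss visit 7. The asymmetry is between on-schedule women.
- **Counting as event-free is not stated.** The article says only that the safety set is all randomized women and that nothing is imputed. If an early-closed woman stays in that denominator she would appear as a non-event, but this is an inference. The SAP, not shown, may treat incomplete follow-up otherwise.
- **Few components are at risk.** Spontaneous abortion, stillbirth, the preterm pathways and antenatal bleeding are settled by delivery.

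These points reduce the likely size. They do not explain why the two windows differ at the lower end, and an analysis plan cannot recover outcomes that were not collected.

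**Conclusion.** The point holds as a difference in permitted ascertainment. Followed exactly, the schedule lets a group A woman be closed up to 14 days before the primary maternal endpoint ends, while an on-schedule group B woman cannot be closed before it ends. For most group A women visit 10 is the last scheduled maternal-outcome assessment, and outside the immunogenicity subset it ends the trial. The exception is some women who deliver before dose 2.

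The effect is probably small. On the assumptions above it amounts to well under one maternal death per 1000 even in the extreme case, plus an amount for late haemorrhage and post-partum pre-eclampsia/eclampsia that cannot be sized here. A reader might infer that the comparison is materially biased in favour of the vaccine. The documents do not show that. They show only that any events missed through early closure would be missing from the vaccinated arm. With about 2 maternal deaths expected per 1000, a single missed event would be visible in the table, so the correction is worth making.

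**What to change.** Ensure that maternal outcomes are ascertained through at least PP 43 in both arms. Either route is enough:

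1. Remove the minus side of the group A visit 10 window in Table 2. No vaccination is scheduled at that visit, and the group B schedule is untouched.
2. For women seen before PP 43, record maternal outcomes through PP 43, with event dates, at infant visit 3 (PP 99 ± 14 days), or by a call where there is no live infant. This route also covers women already seen early.

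In either case, state that primary maternal events count only to the same 42-day cut-off in both arms, because the upper ends of the two windows also differ (56 and 70 days).

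The cost is one edited window or one added question. Some group A women would attend up to two weeks later than they otherwise would, or answer one extra question. The second route relies on recall at 12 to 16 weeks, so the first is cleaner for women not yet seen. Sample size does not change.
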